### Participant Safety and Ethical Considerations

The quality of the water will be routinely observed and recorded. Until medically cleared, children with open wounds, central lines, or symptoms of skin infections will not be allowed to participate in aquatherapy. Before each session, a pediatric oncologist will check all participants for symptoms of fever or active infections. For emotional support during the first sessions, parents or other caregivers may be present. The research ethics board will be notified of all adverse events, mild or major. Before participating, families will be briefed on any possible dangers and asked to sign a form providing informed consent and assent. Periodically, a data safety monitoring team will examine events and make necessary protocol adjustments.

### Consumer Perceptions

Semistructured interviews will be conducted twice before the intervention (week 0) and after the intervention (week 4), with participants in the aquatherapy group to explore their experiences with the program. A purposive sample of participants will be asked about satisfaction, perceived benefits, and the ease of participating in aquatherapy. The same group will be interviewed at both time points. Interviews will continue until data saturation is reached and no new themes emerge.

### Sample Size Estimation

It is estimated that 54 participants will be required [1].

Sample size calculation for paired means (before-after) functional mobility.

The following formula was used:

n ≥ [2(Z_1–α/2_ + Z_1–β_)^2^ / (δ_diff / σ_diff)^2^] + Z_1–α/2_^2^ / 2

Z_1–α/2_ = 1.96

Z_1—β_ = 1.64 at 95% power

The mean difference (δ_diff) was 1.12 before and after the results as per the reference article. The SD (σ_diff) was 1.09.

n = 2 × (1.96 + 1.64)^2^ / (1.12 / 1.09)^2^ = 24.55 = (1.96^2^) / 2 = 1.92

The sample size was 26.47≈27, and the minimum paired sample size needed was 27 for each group.

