The primary aim of this randomized controlled trial is to determine the comparative efficacy of aquatherapy versus conventional physiotherapy on motor function in children with ALL during the induction and consolidation phase of their chemotherapy treatment. The secondary aims include determining the comparative efficacy of aquatherapy versus conventional physiotherapy on the (1) psychosocial well-being and (2) quality of life of children with ALL during the induction and consolidation phase of their chemotherapy treatment.

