## Discussion

### Anticipated Findings

The functional mobility and balance of children receiving therapy for ALL can be improved by a tailored intervention, as per this study. Our results could be consistent with earlier studies that demonstrate the advantages of virtual reality and exercise-based therapies in pediatric oncology rehabilitation [1]. Rehabilitation techniques have been found to improve balance and motor function impairment resulting from chemotherapy-induced neurotoxicity, such as vincristine-induced peripheral neuropathy [5]. Physical activity during cancer therapy has been found to reduce some of the adverse effects of ALL treatments [6]. Furthermore, research on the effects of exercise programs, such as aquatherapy and plyometric exercises, has shown that children who have survived cancer have significantly increased bone mineral density and functional capacity [13]. This study proposes that children receiving treatment for ALL may benefit in terms of physical health from structured movement-based therapy.

These findings have clinical relevance as they support the value of structured rehabilitation programs in pediatric oncology settings. Prior research has highlighted the need for incorporating exercise therapies into standard cancer care to improve overall survival and quality of life [13]. The study suggests how aquatherapy can improve motor function, balance, and general physical activity in this susceptible group when the intervention is conducted in the induction and consolidation stages of treatment. Exercise therapies have been shown to dramatically improve physical results in children with ALL, and aquatherapy may provide extra advantages because of its supportive setting, which promotes mobility while reducing joint stress. This study may prove beneficial for developing evidence-based rehabilitation plans that improve the functional recovery and quality of life for young patients with ALL.

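### The stated 95% power is not established for the aquatherapy-versus-physiotherapy comparison, because the sample size uses a before-after change and no between-arm difference is stated

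*Protocol article*

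**What the plan says.** The Sample Size Estimation section heads its formula "Sample size calculation for paired means (before-after) functional mobility". On the inputs it says: "The mean difference (δ_diff) was 1.12 before and after the results as per the reference article" and "The SD (σ_diff) was 1.09". The normal quantiles are "Z_1–α/2_ = 1.96" and "Z_1—β_ = 1.64 at 95% power". It concludes that "the minimum paired sample size needed was 27 for each group", which gives the total of 54.

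The primary aim, at the end of the Introduction, is to "determine the comparative efficacy of aquatherapy versus conventional physiotherapy on motor function in children with ALL". The Statistical Analysis section tests this with an independent t test or a Mann-Whitney U test, with analysis of covariance as an option. The primary end point is at week 4 (Study Outcomes).

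Table 1 gives the comparison group five supervised 45-minute sessions a week for 4 weeks, including strengthening, resistance and balance work. The Discussion (Anticipated Findings) states: "Exercise therapies have been shown to dramatically improve physical results in children with ALL".

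**The concern.** A before-after change and a difference between randomised arms are different quantities. The first includes whatever improvement both arms share; the second is what remains after the comparator's own improvement is taken away. The plan quantifies only the first, and then attaches 95% power to a trial whose purpose is the second. With an active comparator, and the protocol's own statement that exercise helps these children, the two cannot be assumed equal without argument.

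The calculation is the only stated justification for 54 participants. If it stands, a non-significant result could be read as a negative finding from a trial with 95% power, although power for a plausible difference over active physiotherapy might be far lower.

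**Working it through.** **Inputs (Sample Size Estimation).** Mean before-after difference 1.12 (unit and arm not stated); SD of that difference 1.09; z = 1.96 (two-sided 5%); z = 1.64 (95% power).

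**1. Reproduce the plan's figure.**
- Standardised difference: 1.12 / 1.09 = 1.0275; its square is 1.0558.
- Main term: 2 × (1.96 + 1.64)² / 1.0558 = 2 × 12.96 / 1.0558 = 24.55.
- Added term: 1.96² / 2 = 1.92.
- Sum: 26.47, rounded up to 27. The figure reproduces.

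**2. Which design does the formula describe?** A calculation for paired means has no factor 2: 12.96 / 1.0558 + 1.92 = 12.28 + 1.92 = 14.20, so 15 pairs. With 27 pairs, a paired t test on these inputs has about 99.9% power. The factor 2 belongs to a comparison of two independent groups. The plan therefore joins a paired label and paired inputs to a two-group multiplier, and the 95% fits only the two-group reading.

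**3. Power of the two-group test.** Two-sample t test (noncentral t), two-sided 5%, SD of change 1.09. The noncentrality parameter is (difference / 1.09) × √(n/2), with n per group. The documents give no between-arm difference, so fractions of 1.12 are assumed to show the sensitivity. The 23 per group is also an assumption (15% loss: 27 × 0.85 = 22.95).

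| Between-arm difference in change | Share of 1.12 | Power, 27 per group | Power, 23 per group |
|---|---|---|---|
| 1.12 | 100% | 96% | 93% |
| 0.84 | 75% | 79% | 72% |
| 0.56 | 50% | 46% | 40% |
| 0.28 | 25% | 15% | 14% |

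**4. What the planned size can detect** (same test and SD).

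| Power | 27 per group | 23 per group |
|---|---|---|
| 95% | 1.09 | 1.19 |
| 90% | 0.98 | 1.07 |
| 80% | 0.85 | 0.92 |

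**5. Which outcome scale does SD 1.09 fit?** It is the SD of a before-after difference. With equal variances at both visits and correlation r between them, SD of change = SD of score × √(2(1 − r)), so SD of score = 1.09 / √(2(1 − r)). The two are equal only at r = 0.5. For an independent t test on raw week-4 scores, 27 per group and a difference of 1.09 (r assumed):

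| r | SD of week-4 score | Power |
|---|---|---|
| 0.5 | 1.09 | 95% |
| 0.7 | 1.41 | 80% |
| 0.8 | 1.72 | 63% |

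A restated calculation that keeps SD 1.09 must therefore refer to change from baseline.

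**The case against.** The strongest reply is that the number is usable as it stands. Because of the factor 2, 27 per group is a valid two-group size, and power is about 96% if the arms differ by 1.12 in change. That stands. A reader might infer that the trial lacks its stated power. The documents do not show this, because the true between-arm difference is unknown.

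A reader might also infer that 1.12 is the change in a single arm, so that the plan assumes no change at all under physiotherapy. The before-after label makes this the natural reading, but the section names no arm and the reference article is not at hand. The zero-change consequence follows only if 1.12 is one arm's change.

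Nor can the 95% be dismissed as belonging to a question the trial does not ask. The Statistical Analysis section does plan within-group before-after tests, although they do not address the primary aim; and 27 pairs would give about 99.9% for such a test, not 95%.

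The contrast itself is not settled. The Experimental Group section gives aquatherapy in addition to conventional physiotherapy, whereas the Intervention section describes guidance through aquatherapy sessions alone. These passages must be reconciled, since they determine what the between-arm difference means. On either reading it is a difference between two treated arms.

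Finally, the fractions of 1.12 and the 15% loss have no source in the documents. They show sensitivity and do not estimate this trial's power. The absence of a stated allowance for loss carries no weight in the conclusion, as a condensed article may leave that to the full protocol.

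**Conclusion.** The concern holds as a mismatch between the sample size basis and the randomised comparison. The arithmetic is right, but the effect is a before-after change, the label is paired, and no difference between the arms is stated or justified. The 95% power is therefore not established for the primary comparison, which is a weaker statement than saying it is absent. It holds (about 96%) only if the arms differ by the full 1.12 in change. With 27 per group, power drops below 95% once that difference is under about 1.09, and below 80% once it is under about 0.85. At half of 1.12 it is about 46%.

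These figures assume that SD 1.09 applies to change in both arms, that all 27 per group are evaluable, and that the test is a two-sided 5% two-sample t test on change. This should be corrected before the trial reports, because it is the only stated basis for the size.

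**What to change.** Keep 54 participants. In Sample Size Estimation, delete the paired before-after label and the description of 27 as a paired sample size. Restate the calculation as a two-group one on the primary comparison, for example:

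*With 27 evaluable participants per group, the trial has 95% / 90% / 80% power to detect a between-arm difference in change from baseline to week 4 in the timed up and go test of 1.09 / 0.98 / 0.85 (SD of change 1.09, two-sided 5%). With 23 evaluable per group (15% loss, assumed), the corresponding differences are 1.19 / 1.07 / 0.92.*

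Give the unit of these differences, and say which of them would matter for a comparison with active physiotherapy, since detectable differences alone do not supply that. Keep the 95% claim for 1.12 only if 1.12 is justified as the difference over physiotherapy.

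In Statistical Analysis, have the between-group test use change scores, or analysis of covariance with baseline as covariate, so that it matches the SD in the calculation.

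The cost is wording only, with no extra patients or visits. The price is a less favourable statement of power.

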## Results

The trial has not yet commenced and will commence in October 2025.

## Discussion

### Anticipated Findings

The functional mobility and balance of children receiving therapy for ALL can be improved by a tailored intervention, as per this study. Our results could be consistent with earlier studies that demonstrate the advantages of virtual reality and exercise-based therapies in pediatric oncology rehabilitation [1]. Rehabilitation techniques have been found to improve balance and motor function impairment resulting from chemotherapy-induced neurotoxicity, such as vincristine-induced peripheral neuropathy [5]. Physical activity during cancer therapy has been found to reduce some of the adverse effects of ALL treatments [6]. Furthermore, research on the effects of exercise programs, such as aquatherapy and plyometric exercises, has shown that children who have survived cancer have significantly increased bone mineral density and functional capacity [13]. This study proposes that children receiving treatment for ALL may benefit in terms of physical health from structured movement-based therapy.

These findings have clinical relevance as they support the value of structured rehabilitation programs in pediatric oncology settings. Prior research has highlighted the need for incorporating exercise therapies into standard cancer care to improve overall survival and quality of life [13]. The study suggests how aquatherapy can improve motor function, balance, and general physical activity in this susceptible group when the intervention is conducted in the induction and consolidation stages of treatment. Exercise therapies have been shown to dramatically improve physical results in children with ALL, and aquatherapy may provide extra advantages because of its supportive setting, which promotes mobility while reducing joint stress. This study may prove beneficial for developing evidence-based rehabilitation plans that improve the functional recovery and quality of life for young patients with ALL.

### Conclusions

Aquatherapy is a rapidly growing area that may have many positive impacts among individuals with ALL undergoing chemotherapy. This trial has the potential to inform future models of cancer rehabilitation mainly aquatherapy intervention, which can be implemented in health services to improve access to aquatherapy for patients with ALL.

## Appendix

Multimedia Appendix 1 SPIRIT (Standard Protocol Items: Recommendations for Intervention Trials) checklist.

Multimedia Appendix 2 Institutional ethics committee certificate.

Multimedia Appendix 3 Clinical Trial Registry India registration.

Multimedia Appendix 4 Informed consent form.

## Abbreviations

ALL: acute lymphoblastic leukemia
CONSORT: Consolidated Standards of Reporting Trials
SPIRIT: Standard Protocol Items: Recommendations for Intervention Trials
WeeFIM: Functional Independence Measure for Children
